**Future Orientation**

We will use the 15-item Future Outlook Inventory developed by Cauffman and Woolard ([Cauffman & Woolard, 1999](#_ENREF_13)). The inventory uses items from the Life Orientation Task (Scheier & Carver, 1985), the Zimbardo Time Perspective Scale (Zimbardo, 1980), and the Consideration of Future Consequences Scale (Strathman, Gleicher, Boninger, & Edwards, 1994). Initial psychometric properties for this measure were established with a non-incarcerated sample. With that sample, the reliability coefficient = .71 and the measure correlated with self-reports of risk perception among high school and college students.

The Future Outlook Inventory asks participants to rank from 1 to 4 (1= Never True to 4= Always True) the degree to which each statement reflects how they usually are (e.g., I will keep working at difficult, boring tasks if I know they will help me get ahead later). Higher scores indicate a greater degree of future consideration and planning.

The Future Outlook Inventory will be supplemented with the six-item revised Life Orientation Test (LOT-R) ([Scheier, Carver, & Bridges, 1994](#_ENREF_80)). The six item version showed internal reliability (α = .78) and was found to be fairly stable over time with samples of U.S. college students.

**Social Cohesion**

We will use an adapted measure of social cohesion developed by Sampson, Raudenbush & Earls ([R. J. Sampson, Raudenbush, & Earls, 1997](#_ENREF_78)). Participants will respond to statements related to cohesion of camp members on a 4-point Likert scale ranging from 1 = strongly disagree to 4 = strongly agree. The statement included “people in my camp are willing to help each other” and “the members of my camp share the same values”. Two negatively framed questions will be reversed to the positive for ease of use. Kim et al. used a similar measure of social cohesion in an analysis of the relationships between neighborhood collective efficacy and adolescent sexual behavior in the US ([J. Kim, 2010](#_ENREF_42)).

**Collective efficacy** (Reciprocated Exchange)

Collective efficacy measures the extent to which people believe in their ability to act cooperatively to solve problems. Our goal in providing microfinance opportunities to camp members is to enhance the camp’s collective efficacy to achieve similar health outcomes. We will use the 5-item collective efficacy measure of reciprocated exchange (alpha = .65) ([R.J. Sampson, Morenoff, & Earls, 1999](#_ENREF_77)), which has been validated in other settings. For our measure we will substitute the word “neighborhood” with “camp,” and add a question about the frequency with which camp members visit their camp. Participants will be asked how often activities takes place within his camp on a 4-point Likert scale from 1 = Very Often to 4 = Never. Activities included having get-togethers as well as asking each other advice about personal things. To assess reciprocated exchange, each participant was asked how often a set of six activities takes place within his camp. Activities included having get-togethers as well as asking each other advice about personal things.

**Emotional Distress**

The HSCL-25 ([Hesbacher, Rickels, Morris, Newman, & Rosenfeld, 1980](#_ENREF_31)) includes the anxiety and depressive dimensions of the HSCL-58, derived from the Symptom Checklist-90 and originally developed by Derogatis *et al.* ([Derogatis, Lipman, Rickels, Uhlenhuth, & Covi, 1974](#_ENREF_16)). The items are scored on a scale from 1 (not bothered) to 4 (extremely bothered), and a mean score of 1.75 has been defined as the cut-off point for ‘caseness’ ([Winokur, Winokur, Rickels, & Cox, 1984](#_ENREF_98)) and has been validated for Southeast Asian versions of the HSCL-25 ([Mollica, Wyshak, de Marneffe, Khuon, & Lavelle, 1987](#_ENREF_58)).

We will use a version of the HSCL 25 translated into Kiswahili and implemented in Tanzania ([Lee, Kaaya, Mbwambo, Smith-Fawzi, & Leshabari, 2008](#_ENREF_48)). The measure inventories symptoms of anxiety and depression in 25 items (10 related to anxiety, 15 to depression). When implemented in antenatal clinics, the measure showed Good internal consistency for the total scale (a = 0.90) and for the depression subscale (a = 0.88), but marginal internal consistency (a = 0.76) for the anxiety subscale. Participants will respond to how much symptoms bothered them on a 4-point Likert scale from 1 = Not at All to 4 = Extremely.

**Work and Expenditures**

Questions on work and expenditures will be incorporated to assess changes in participants exposed and not exposed to the microfinance component. These questions will be derived from the Tanzania National Panel Survey’s (TNPS) Multi-topic Household Questionnaire ([W. Bank, 2012](#_ENREF_7)). Design and implementation of the TNPS is supported by the Living Standards Measurement Study-Integrated Surveys on Agriculture. Only questions relating to work and expenditures will be included.

**Adverse Childhood Experiences**

We will assess adverse childhood experiences during participants’ first 18 years of life using the Adverse Childhood Experiences International Questionnaire (ACE-IQ). This includes questions adapted from the Conflict Tactics Scale. For categories adapted from the CTS, response categories are “never,” “once” “a few times,” “many times.” The ACE-IQ includes questions on 13 categories of adverse childhood experiences: emotional abuse; physical abuse; sexual abuse; violence against household members; living with household members who were substance abusers; living with household members who were imprisoned; growing up with one or no parents; parental separation, or divorce; emotional neglect; and bullying. Though the measure is relatively new, it has been field tested in China, the Philippines, Saudi Arabia, South Africa, and Vietnam. It is currently being validated in six countrywide studies and has shown to be positively correlated with adverse health conditions in Vietnam (Tran et al., 2015).

**Household Hunger**

We will use four items from the Household Food Insecurity Access Scale (HFIAS), developed by FHI 360 through USAID’s Food and Nutrition Technical Assistance (FANTA) project. The scale has been used in several countries and can be used to assign households, individuals, and populations to a level of food insecurity, from food secure to severely food insecure. The scale was validated by Kneuppel et al. in Tanzania, where it showed good internal consistency (Cronbach’s a = 0.90) among a sample of 237 households and 21 key informants. Construct validity was verified in the same sample through factor analysis, with constructs explaining 69% of variance. Food security was positively associated with education and household wealth status and negatively associated with maternal age and household size (Kneuppel et al., 2009)

## 7.6 Process Outcomes

Intervention process outcomes and monitoring data collection will occur throughout the life of the study. Monitoring data will be collected ongoing through the two year intervention period. Additional process outcomes will be collected during behavioral data collection at midpoint and endpoint.

### 7.6.1 Microfinance Process Outcomes

Data will be collected during midpoint and endpoint surveys to assess rationale for loan uptake or non-uptake and effects of accessing the loan. Microfinance borrowers will be asked about businesses they started or supported with the loan, how they have benefited or suffered from taking the loan, and reasons for any difficulties in repaying the loan.

### 7.6.2 Microfinance Monitoring

Data will be collected at each weekly repayment session to monitor microfinance participation and repayment success. These data will be aggregated at the camp level to compare with other camps. Data to be collected on this form include:

**Attendance**

Data will be collected at weekly loan repayment meetings on whether or not individuals accessing loans attended weekly mandatory meetings.

**Loan Acquisition**

We will keep a roster for all camp members eligible for the microfinance intervention (completed baseline survey), and compare this to the total number of individuals who fulfill requirements and access loans.

**Loan Repayment**

Data will be collected at weekly loan repayment meetings on whether or not individuals paid installments. We will also monitor individuals who have completely paid back loans.

**Savings Deposited**

Participants accessing loans are required to contribute to personal savings for reserve in case of non-payment, and encouraged to deposit additional savings each week. We will monitor cumulative savings deposited.

**Loan Default and Dropout**

Repayment data will be monitored over time to determine whether or not individuals defaulted on their loan. We will also monitor participants that accessed a loan, repaid the loan completely, but decided not to access further loans.

**Types of businesses**

We will assess the type of businesses that men initiate with their microfinance loans.

**Profit earned from business**

We will assess how much profit, if any, men have earned from their business.

### 7.6.3 Camp Health Leadership Process Outcomes

Data will be collected at midpoint and endpoint to assess leadership characteristics of Camp Health Leaders and their reach in implementing the health leadership portion of the intervention. These questions were developed from a review of numerous publications on peer leadership ([Flanagan, Williams, & Mahler, 1996](#_ENREF_25); [Mason-Jones, Flisher, & Mathews, 2011](#_ENREF_53); [Pearlman, Camberg, Wallace, Symons, & Finison, 2002](#_ENREF_62); [Perry, Klepp, Halper, Hawkins, & Murray, 1986](#_ENREF_63)).

Nominated CHL will be shown a list of people they know in their camps and asked who on the list they have talked with about HIV or GBV. CHL will then be asked the frequency of HIV or GBV questions in the week prior to the assessment. Leadership characteristic questions will include CHL confidence in conversing about HIV and GBV, as well as how much they agree that the CHL training increased their knowledge of HIV and GBV, interpersonal skills, compassion towards others, and leadership skills. CHL will also be asked about their comfort in their role as CHL and talking about HIV and GBV, as well as whether they believe they are taken seriously in their role.

### 7.6.4 Camp Health Leaders Monitoring

We will ask health leaders to record the number and types of the conversations that they have with camp members related to HIV and GBV. CHL will be provided diaries divided by week and asked to record the number of individual(s) talked to, how many were male and female, the topic of conversation, and any challenges encountered. Records of conversations will be collected bi-weekly at loan repayment meetings or by visiting CHLs at camps. Urgent challenges will be followed up with phone calls, and trainers will use non urgent challenges to generate topics for booster sessions.

## 7.7 Qual*i*tative Outcomes

We will conduct 3 focused qualitative studies through the life of the project with a sub-sample of eligible and consenting participants. Each study will have a different focus pertaining to HIV risk, GBV perpetration, or intervention experience. Qualitative study topics include:

1. Intimate Partner Violence
2. Leadership and Microfinance
3. Childhood Experiences and Adult Conflict

The study team will convene during the intervention period and at the end of the intervention period to review interview transcripts and develop a coding scheme that identifies broad themes and subthemes related to the study’s research questions. Members of the study team will read the transcripts multiple times to refine the codes and will practice using the coding scheme on a selection of transcripts to ensure that all relevant text is captured appropriately by a code. After the coding scheme has been developed, a staff of coders will be trained to apply the codes to the transcripts. To ensure intercoder reliability, a subset of data will be double-coded. The study team will resolve coding discrepancies. Codes will be entered into ATLAS.ti. Using these codes, the study team will retrieve and analyze text relevant to the research study questions.

# 8. DATA COLLECTION AND ADVERSE EVENT REPORTING

Both quantitative and qualitative data will be collected, and we have developed a data management plan for each. Quantitative data will include results from the baseline demographic and behavioral survey, follow-up behavioral data collected at months 12 and 30, and STI assessments at baseline and month 30.

## 8.1 Data Management Center

The study team at the University of North Carolina at Chapel Hill will serve as the Data Management Coordinating Center. All behavioral and biological data will be entered on Samsung galaxy tablets and compiled by the Data Manager in Delhi, India. UNC study staff will work with the Data Manager to ensure the proper collection, storage, and transfer of data to UNC for cleaning and analysis.

## 8.2 Quantitative Data Management Plan

### 8.2.1 Data Security

The CAPI system we are using for survey collection and STI results has multiple tiers of security. A password must be entered to activate the tablet computer and a second password must be entered to access the data capture software.  There are different levels of access for interviewers, field supervisors, and system administrators.  Only users with administrator level access will have the ability to delete data that had been previously captured.  The data captured on the device will be in a machine-readable (xml) format and is not easy to interpret without using a computer program. In such a case, data stored on the device is archived in a separate directory and is encrypted using 128 bit AES encryption. Thus, any data stored on the device is inaccessible unless decrypted. The decryption key is not stored on the device and is maintained by the central data management team. There is also an option available to delete the data from the device after uploading to the Data Manager. As an additional security measure, lost or stolen tablets can be tracked and have their data erased remotely by data management staff in India when the lost or stolen tablet is connected to a Wi-Fi or cellular network.

All data captured by the tablets will be transmitted to the database server based in India using HTTPS, which is a widely used communications protocol for secure communication over a computer network. HTTPS provides authentication of the web app and associated web server that one is communicating with, which protects against malicious attacks. Additionally, it provides bidirectional encryption of communications between a client and server, which protects against eavesdropping and tampering with and/or forging the contents of the communication.

Once the data reaches the data server, it is then stored on a secure server. The server support RAID-1 storage in which a complete copy of the data is stored on multiple independent disk drives as a precaution against disk failure. The database is configured to make automated backups and logs of all modifications.  Additional monthly backups of the database are stored on external media such as DVD disks, which are under lock and key. Access to the server and database are restricted to authorized personnel with a valid password.

#### 8.2.2 Data Transfer and Analysis

Behavioral data collected on Samsung Galaxy tablets will be compiled by the Data Manager in Delhi, India. Following each phase of data collection the de-identified data will be sent to UNC and MUHAS in password protected files for cleaning and validation. Study staff from UNC will coordinate with field staff in Tanzania to clean and validate the data. Cleaned and validated data will be kept at UNC for analysis using SAS SURVEYLOGISTIC version 9.2. Analyses will be shared via password protected files with field staff. Data files will not contain identifying information on study subjects, but will contain a Personal Identification number to allow for checking of original paper forms for errors that might be identified.

All members of the study team potentially involved in data cleaning, analysis, or interpretation will be guided by a set of principles: (1) timely and rigorous analysis and dissemination of study data is a major responsibility the project has to the study participants and the research field, (2) project members should submit brief concept sheets using a standard forms proposing analyses that they wish to take the lead on, (3) other individuals may be given the opportunity to become involved in proposed analyses at the discretion of project PIs (4) all PIs will be given access to the cleaned data sets, both in the U.S. and in host countries, (5) data dispersed to project team members will be blinded of any identifying information to assure confidentiality, (6) there will be an opportunity to review all papers published from the project by all PIs, (7) there are many important means of dissemination of study results, including publications, presentations at meetings, and also in-country dissemination activities, all which should be supported, (8) that junior members of the overall study team should be given the opportunity to analyze and disseminate data with mentoring by senior members of the team, and (9) that full public access to the raw data should be made in a timely manner once the study has been completed and major papers have been disseminated.

#### 8.2.3 Data Collection Forms

**Community Informant and Camp Verification Interviews**

Community Informant and Camp Verification Interviews will be completed by Research Assistants in the field with pen and paper. The Community Informant form solicits the names of camps from community members of the four study wards. The Camp Verification form collects GPS coordinates and characteristics of existing, active camps found in during the Community Informant interviews. All completed interviews will be collected by the Research Coordinator at the end of each day and delivered to the data entry team at MUHAS for entry in to an Access database. Physical forms will be stored in a locked cabinet in the field office.

**Behavioral Survey**

An approximately 1 hour behavioral survey instrument will be created and formatted in Samsung Galaxy tablets. The survey will be comprised of variables that assess, but are not limited to, demographic data, HIV risk and protective behaviors, social and sexual networks, gender-based violence perpetration and victimization, hope, collective efficacy, emotional distress, social support, alcohol and drug use, and work and expenditures. The behavioral survey form will be used at baseline, and 12 and 30 month follow-ups.

**Participant Contact Form**

Logs of participant contact and survey status will be used to monitor whether or not participants have completed the survey, refused, or follow-up is needed. Similar logs will be kept by nurses to monitor uptake of STI testing among those selected to participate. These forms will be kept in locked cabinets at all times.

**Lab Transport Form**

Lab transport forms will be used to monitor the movement of biological specimens between collection sites, storage sites, and sites of analysis. Forms for each individual participating in specimen collection will receive a de-identified alpha-numeric label to track individual specimens. Lab result forms will be returned to study staff with the same alpha-numeric code to link to behavioral data.

### 8.3 Qualitative Data Management Plan

Study staff are responsible for the development of standardized field guides for the collection and coding of qualitative data. These data will be translated from local language into English and then transcribed and typed into computer files for analysis. Audio recorders will be procured for the study site for use by staff. The Intervention Coordinator will supervise transcription and translation staff, and there will be regular quality assurance checks conducted to assure consistency in methods of translation and transcription. Strict security procedures will be followed to ensure confidentiality and security of qualitative data. The final data files will be shared with U.S. staff via password protected files. Study documentation will be kept in locked files at the field study site. The transcriptionists will be trained to blind any identifying information of study participants as data is entered into textual computer files.

# 9. STATISTICAL CONSIDERATIONS

## 9.1 Quantitative Statistical Analysis Plan

## 9.1.1 Sample Size, Power Calculations and Effect Size

The choice of 60 camps randomized into two groups is based upon evidence generated in our previous study and likely incidence estimates available from published studies with similar populations in Tanzania and other countries in Africa. We estimate average camp sizes of 36.2 sexually active males and 52 total males. STI measures of ulcer, discharge, any symptom, and any STI were used as possible sexual outcome measures, with condom use and sexual and/or physical violence perpetration our behavioral outcome measures. Based upon our previous study we computed intraclass correlation (ICC) estimates between 0.00 and 0.01 for sexually transmitted diseases and 0.00-0.032 for behavioral measures. Given average camp sizes and ICC estimates we have inflated sample size estimates assuming simple random sampling with design effects ranging from 1.4 to 2.3. All sample estimates assumed an attrition of 20%. Given a sample size of 1955 sexually active males and 2808 total males in 54 camps we will have 80% power (2-sided, α=0.05) to detect the protective effect of the intervention (OR) of 0.32 for ulcer, 0.59 for discharge, 0.61 for any STI symptom, 0.50 for syphilis, and 0.66 for any STI. We will be able to detect protective effects of 0.74, 0.68 and 0.65 in condom use for those sexually active, for all males, and for sexual or physical violence perpetration in all males, respectively. Statistical power to detect mediation is expected to be high based on the simulation results of Fritz and MacKinnon where a total sample size of 539 was sufficient for .80 power to detect the most conservative simulated mediation effect.([Fritz & MacKinnon, 2007](#_ENREF_27))

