# PROTOCOL SUMMARY

**Purpose:** The purpose of this study is to determine whether men in camps randomized to receive a microfinance and health leadership intervention have a lower incidence of sexually transmitted infections (NG, TV, CT) and report perpetrating less physical or sexual violence against female sexual partners as compared to men in camps not randomized to receive the intervention.

**Design:** Cluster-randomized trial.

**Study Population:** Young men ages 15 or older that are members of camps (social groups) in Dar es Salaam, Tanzania.

**Study Size:** 1249 male camp members

**Intervention:** 60 eligible camps will be randomized in to either a microfinance and health leadership intervention or a control condition. Eligible members in the intervention camps will be able to participate in intervention activities.

**Duration and Follow-up:** This a 5 year cluster-randomized study. Behavioral data will be collected at baseline, 12 months, and 30 months after intervention. Biological data will be collected at baseline and 30 months.

**Primary Objectives:** To determine whether men in camps randomized to receive a microfinance and health leadership intervention have a lower prevalence of sexually transmitted infections (NG, TV, CT) and report perpetrating less physical or sexual violence against female sexual partners as compared to men in camps not randomized to receive the intervention.

**Primary Endpoints:** Incidence of STIs (NG, TV, CT) and perpetration of sexual violence against female sexual partners.

**Secondary Endpoints:** HIV risk and protective behaviors including: gender equity, alcohol and drug use, sexual relations and risk behavior, uptake of HIV counseling and testing; unprotected sexual intercourse; consistent condom use; delay of sexual debut; number of sexual partners, and sexual concurrency.

**Mediators**: In the event that program effects are identified, the degree to which the following mediate the multi-level intervention on STI and gender-based violence: hope, future orientation, social cohesion, collective efficacy, social support, emotional distress, sexual networks, social support and social influence.

**Qualitative:** Qualitative interviews with study participants will add contextual data for understanding various aspects of participant beliefs, attitudes, and behaviors towards endpoints measured.

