### 3.2.3 Second Primary Aim

To achieve our second primary aim, to evaluate the efficacy of a combined microfinance and health leadership intervention we will conduct a trial among 1252 men in 60 camps that are randomly selected proportionally across four wards. Our primary hypothesis is that the combined microfinance and health leadership intervention will be associated with a lower incidence of sexually transmitted infections and other HIV risk behaviors and less perpetration of violence against female sexual partners over time among men in camps randomized to the intervention as compared to men in camps randomized to the control condition. We also hypothesize that men’s hope for, and orientation towards, the future, as well as the support, social influence and the collective efficacy of their networks, will mediate the effect of the intervention on these outcomes.

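### The 80% power in Protocol 9.1.1 is calculated for 1,955 or 2,808 men in 54 camps, not for the planned 1,249 or 1,252 men in 60 camps, and no figure is tied to NG, CT or TV by PCR

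*Protocol*

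**What the plan says.** Protocol 9.1.1 opens by justifying "The choice of 60 camps randomized into two groups". It assumes "average camp sizes of 36.2 sexually active males and 52 total males" and ICC "estimates between 0.00 and 0.01 for sexually transmitted diseases and 0.00-0.032 for behavioral measures", with design effects from 1.4 to 2.3 and 20% attrition. It then claims, for a two-sided test at α = 0.05: "Given a sample size of 1955 sexually active males and 2808 total males in 54 camps we will have 80% power".

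The detectable odds ratios listed are 0.32 for ulcer, 0.59 for discharge, 0.61 for any STI symptom, "0.50 for syphilis, and 0.66 for any STI", 0.74 and 0.68 for condom use, and 0.65 for physical or sexual violence. The section gives no control-arm rates.

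The study size is "1249 male camp members" in the Protocol Summary and "a trial among 1252 men in 60 camps" in 3.2.3. Sections 3.3 and 7.2 set the primary STI endpoint as NG, CT and TV, tested by PCR on urine. Section 7.2 describes blood testing for HIV only. All men are to be tested at endline (3.3, 6.6).

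**The concern.** The power paragraph describes a trial with more than twice as many men, in a different number of camps. It contradicts the protocol's own study size, so a separate analysis plan would not cure it. A reader who sees a null result could take the trial as having had 80% power against odds ratios of 0.65 (violence) and 0.66 (any STI), when that figure was never calculated for this design. For the STI endpoint the reader also cannot tell which printed odds ratio, if any, refers to the NG/CT/TV outcome.

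**Working it through.** **1. The plan's sample sizes.** 54 × 36.2 = 1,955 and 54 × 52 = 2,808, so both follow from 54 camps. Sixty camps would give 2,172 and 3,120. The trial has 1,249/60 = 20.8 men per camp (1,252/60 = 20.9), and 1,249/2,808 = 44%. Attrition does not explain the gap, since 2,808 × 0.8 = 2,246.

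**2. The plan's design effects.** DE = 1 + (m − 1) × ICC with m = 52 × 0.8 = 41.6 gives 1.41 at ICC 0.01 and 2.30 at ICC 0.032, matching the stated 1.4 and 2.3. For sexually active men, m = 36.2 × 0.8 = 28.96 gives 1.28 at ICC 0.01.

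**3. The 80% itself.** It cannot be reproduced directly without control rates, so I accept it and solve for the control rate p₁ it implies. The formulas are:
- effective n per arm = N × 0.8 / DE / 2
- p₂ = p₁·OR / (1 − p₁ + p₁·OR)
- power = Φ{[|p₁ − p₂|√n − 1.96√(2p̄(1 − p̄))] / √(p₁(1 − p₁) + p₂(1 − p₂))}

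**4. Violence, OR 0.65.** The plan does not say which design effect goes with which outcome; I use 2.3.
- Planned: 2,808 × 0.8 / 2.3 / 2 = 488 per arm. Power of 80% implies p₁ = 0.264 (p₂ = 0.189).
- Actual: 1,249 × 0.8 = 999 men, 16.65 per camp.

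| ICC | DE | n per arm | Power at p₁ = 0.264 | Power at p₁ = 0.41 |
|---|---|---|---|---|
| 0.032 | 1.50 | 333 | 64% | 76% |
| 0.01 | 1.16 | 432 | 75% | 86% |
| 0 | 1.00 | 500 | 81% | 90% |

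At ICC 0.032 and p₁ = 0.264, 80% power needs OR 0.59. Using 1,252 men leaves 333 per arm.

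**5. Any STI, OR 0.66, ICC 0.01.** The sexually active share is 36.2/52 = 70%, so 1,249 × 0.696 × 0.8 = 696 men, 11.6 per camp, DE 1.106, 314 per arm. All men: 999, DE 1.157, 432 per arm.

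| Planned DE | Planned n per arm | Implied p₁ | Sexually active: power (OR for 80%) | All men: power (OR for 80%) |
|---|---|---|---|---|
| 1.28 | 611 | 0.216 | 52% (0.55) | 65% (0.61) |
| 1.4 | 559 | 0.242 | 56% (0.57) | 69% (0.62) |

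**6. Lower STI prevalence (assumption).** At a control prevalence of 5% or 10%, power for OR 0.66 is 18% or 30% in sexually active men, and 23% or 39% in all men.

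None of these figures allows for contiguous camps being assigned together (4.1.4, 4.2). That would lower power further if outcomes correlate within those groups.

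**The case against.** The strongest reply is that the documents do not fix the true power. Section 9.1.1 gives no control rates, and the only violence rate in the protocol (41% ever perpetrating, section 1.7) puts power for OR 0.65 at 76-90%. Smaller camps also reduce the design effect, and testing all men at endline enlarges the STI denominator. All of this stands, and the calculations above credit the trial with the smaller design effect. But the 41% is a lifetime rate from the earlier study and is not named as the power input. The 81% at ICC 0 pairs a control rate derived at design effect 2.3 with no clustering, so it is the favourable end.

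Three stronger readings are tempting and should not be drawn.
- A reader might infer that the trial simply has 50-65% power. That range depends on unstated control rates, on the ICC and on the denominator.
- A reader might infer that only symptoms and syphilis were powered. The list also contains any STI, which may be meant as the NG/CT/TV outcome but is not defined, and the co-primary violence outcome.
- A reader might infer that the condom-use OR of 0.74 is impossible on the plan's own inputs. With 1,955 × 0.8 / 1.4 / 2 = 559 per arm, the OR closest to 1 detectable at any base rate is 0.715. But if 1,955 is already net of attrition, 1,955 / 1.4 / 2 = 698 per arm reaches 0.741, and at ICC 0 with attrition, 782 per arm reaches 0.753. The text allows these readings.

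It can also be said that a null result would be judged by its confidence interval, and that conduct and analysis do not change. That is fair, but it does not make the printed power statement correct.

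**Conclusion.** Wrong as written. That the 80% belongs to another design follows from the protocol's own figures and needs no assumption: 54 camps against 60, and 2,808 men against 1,249 or 1,252. It is equally plain that no power figure is tied to NG, CT or TV by PCR.

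The size of the shortfall is conditional. Taking the plan's 80% and implied control rates as given, with 20% loss, power at the upper stated ICCs is about 64% for violence and 52-69% for any STI. The odds ratios needed for 80% are then about 0.59 and 0.55-0.62, against the stated 0.65 and 0.66. Violence power rises to about 81% at ICC 0, and to 76-90% at a 41% control rate. STI power falls to 18-39% if prevalence is 5-10%, which is an assumption.

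**What to change.** Restate 9.1.1 for the actual design:
- Give one study size (reconcile 1,249 with 1,252), 60 camps, about 21 men per camp and 20% loss.
- Define the STI outcome as NG, CT or TV by PCR, and say whether all men or sexually active men are analysed.
- Remove the syphilis figure.
- For each primary endpoint, give the detectable odds ratio at 80% power over a stated range of control rates and ICCs.

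This is a wording change with a short recalculation. No extra enrolment is needed. The cost is that the stated detectable effects become less favourable.
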